## Exclusion Criteria

Individuals who meet any of the following exclusion criteria will be excluded from this observational study:

1) Individuals with diabetes other than Type 2 Diabetes (e.g., Type 1 Diabetes, Diabetic Ketoacidosis, Gestational Diabetes, etc.)

2) Individuals who fall under the contraindications for administration according to the approved conditions of Envlo Tab./Envlomet SR Tab.

- Patients with hypersensitivity or a history of hypersensitivity to any component of Envlo Tab. or Envlomet SR Tab.

- Patients with an eGFR less than 30 mL/min/1.73 m²

- Patients with renal impairment with an eGFR less than 60 mL/min/1.73 m², end-stage renal disease, or those on dialysis

- Individuals with moderate to severe hepatic impairment (AST or ALT > 3 times the upper limit of normal, Total Bilirubin > 2 times the upper limit of normal, hepatitis, or liver failure)

- Individuals classified as class III or IV according to the New York Heart Association (NYHA) classification

3) Individuals who have undergone treatment with obesity medications or weight loss drugs, or other treatments (surgery, diet, etc.) leading to unstable weight within 3 months prior to the enrollment date

4) Individuals with mental incapacity

5) Pregnant or breast-feeding women

6) Individuals participating in another clinical study and receiving (applying) investigational drugs or investigational medical devices

7) Individuals deemed unsuitable for participation in this observational study based on the judgment of the investigator (responsible physician)

## Completion and Withdrawal/Dropout of Observational Study

1. **Completion and Termination of Observational Study**

A subject is considered to have completed the observational study upon completing the close-out visit procedures at the 24-week point after their first visit (baseline) and the investigational product administration. This observational study is deemed complete when the last subject finishes their observational study participation.

1. **Withdrawal/Dropout of Observational Study**

Subjects can discontinue their participation in the study at any time at their discretion. The investigator or sponsor can also withdraw or drop a subject’s participation at any time for safety, behavioral, or administrative reasons. If a subject is withdrawn/dropped due to an AE, every effort should be made to follow the course of the AE in the subject. The following are conditions under which a subject might be withdrawn/dropped from the study, and the investigator shall enter the collected study data into the eCRF up to the point of withdrawal/dropout:

A subject may be withdrawn or dropped from the observational study if:

1. A subject not meeting the inclusion/exclusion criteria was discovered during the observational study
2. Adverse Event(AE)

: If the investigator determines that it is difficult to continue the observational study due to an adverse event

1. Withdrawal by Subject (or his/her legal representative)
2. Non-Compliance with Investigational Product

: Subjects do not agree to or follow the investigator’s instructions related to the investigational product.

1. Lost to Follow-Up

: Subjects cannot be contacted for follow-up

1. Physician Decision

If a subject is withdrawn/dropped, the investigator must notify the sponsor and make every effort to complete the end-of-observation study evaluation. The reasons for dropout will be recorded in the electronic-case report form (eCRF) and the subject’s source document. Any withdrawn subject cannot participate in the same study again.

## Termination of Observational Study

The principal investigator and the investigator (IRB-approved and delegated by the principal investigator) may, in consultation with the study sponsor, decide to terminate early or temporarily suspend the observational study if it is deemed undesirable to continue based on the results collected during the study process. The sponsor may also terminate the observational study early for safety or administrative reasons. The principal investigator must promptly report this to the IRB and provide detailed reasons for the early termination or suspension.

Reasons for study termination by the sponsor are as follows:

1. Cancellation or suspension of the marketing authorization of the investigational product.
2. The sponsor determines that continuing the study is not medically or ethically justified.
3. Excessive delays in subject recruitment makes it difficult to proceed with the study.

In the event of early termination or temporary suspension for any reason, the investigator must inform the subjects and ensure appropriate actions and follow-up observations are carried out. The investigator must summarize and report the status and results up to the point of termination in the eCRF and provide this information to the sponsor.

# Method of Observational Study

## Overall Design of Observational Study

This observational study is designed as a prospective, multicenter observational study to confirm the weight loss efficacy and safety of Envlo Tab. or Envlomet SR Tab. over 24 weeks in patients with Type 2 Diabetes in real-world primary care settings.

The study plans to recruit patients with Type 2 Diabetes who are scheduled to receive Envlo Tab. or Envlomet SR Tab. based on the medical judgment of the investigator (responsible physician) and in accordance with the approved indications (effectiveness ∙ effect, administration∙ and dosage, precautions for use, etc.) in real-world clinical settings.

Regardless of whether they are currently undergoing pharmacotherapy for diabetes, all eligible patients who are considered suitable for Envlo Tab./Envlomet SR Tab. can be enrolled in this study. However, despite the decision to administer Envlo Tab./Envlomet SR Tab., observation is only possible with the subject's voluntary consent to participate in the study as determined by the investigator's medical judgment.

This observational study will collect demographic information, physical measurement, vital signs, and other relevant information up to 24 weeks after the administration of Envlo Tab./Envlomet SR Tab. in real-world clinical settings, irrespective of whether the medication is administered or not. Data will be collected based on medical records documented in real-world clinical settings. There are no mandatory visits, tests, or treatments specifically required by this observational study.

However, follow-up investigations will be conducted to collect prospective data at 12 weeks (±2 weeks) and 24 weeks (±2 weeks) from the date of subject registration (Visit 1, Baseline, Day 0), depending on the clinical setting. The data to be collected includes basic clinical information such as age and gender, past and current medical history (hypertension, dyslipidemia, diabetes, cardiovascular and cerebrovascular disease, cancer, etc.), lifestyle habits (smoking, alcohol consumption, physical activity), prior and concomitant medications (diabetes, hypertension, dyslipidemia, etc.). Additionally, clinical indicators such as weight, body composition analysis metrics (BMI, body fat mass, muscle mass), fasting blood glucose, HbA1c, blood pressure (systolic/diastolic), total cholesterol, LDL cholesterol, HDL cholesterol, triglycerides, and safety assessment items such as vital signs, laboratory tests, and adverse events will be collected. During the study, the investigator will collect the necessary data based on the information gathered during routine clinical care.

[figure not shown]

Visit 1

(0 days)

Visit 3

(24±2 weeks)

Visit 2

(12±2 weeks)

Baseline

Follow-Up Visits

Close-Out Visit (COV)

Figure 1. Observational Study Flowchart

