# Objective of Observational Study

This observational study aims to verify the weight reduction effects and safety of Envlo Tab. or Envlomet SR Tab. in patients with Type 2 Diabetes over a 24-week period in a real-world clinical setting.

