## Rationale

This study is a large-scale, prospective, multicenter, non-interventional database observational study aimed at observing the weight loss effects, efficacy, and safety of Envlo Tab./Envlomet SR Tab. in patients with Type 2 diabetes over 24 weeks.

As a single-arm observational study, the number of subjects was calculated using G*Power 3.1.9.7, referencing the mean and standard deviation of the changes in weight and body mass index (BMI) from baseline to 12 or 24 weeks from previous Phase 2 and Phase 3 clinical studies (Figure 2) ^20)^

[Assumptions]

- Effect size: 0.25 (Mean of difference 2.5, SD of difference 10.0)
- Power: 0.95
- α error: 0.05
- Drop-out rate: 30%

[figure not shown]

Figure 2. Sample Size Calculation (G*Power)

Based on previous studies, assuming an average weight change of 2.5 kg and a standard deviation of 10.0 for the intervention with Envlo Tab. or Envlomet SR Tab., the effect size is 0.25. Setting the power: 0.95, α error: 0.05, the total required sample size is estimated to be approximately 210 subjects. Considering a drop-out rate of about 15%, we plan to recruit around 240 subjects.

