## Inclusion Criteria

Select individuals who meet all of the following criteria:

1. 1) Adults aged 19 to 80 years, both male ∙and female
2. 2) Patients with Type 2 Diabetes who, based on medical judgment by the investigator (responsible physician) and according to the approved indications, are about to receive Envlo Tab. or Envlomet SR Tab. for the first time

- Enavogliflozin monotherapy

- Enavogliflozin combination therapy with two agents (in combination with metformin)

- Enavogliflozin combination therapy with three agents (in combination with metformin and a DPP4 inhibitor)

1. 3) Patients with pre-obesity or higher stages according to the 2022 Obesity Treatment Guidelines of the Korean Endocrine Society*

* Obesity Treatment Guidelines of the Korean Endocrine Society

- Pre-obesity: BMI 23-24.9 kg/m^2^

- Stage 1 obesity: BMI 25-29.9 kg/m^2^

- Stage 2 obesity: BMI 30-34.9 kg/m^2^

- Stage 3 obesity: BMI >35 kg/m^2^

4) Individuals who plan to engage in appropriate exercise and dietary therapy for blood glucose control during the observational study period

5) Women of childbearing potential and men who agree to use appropriate contraceptive methods* or have no plans for pregnancy during the observational study period

*Hormonal contraceptives, intrauterine device (IUD) or intrauterine system (IUS) implants, vasectomy, tubal ligation, double barrier methods (simultaneous use of cervical cap or diaphragm with male condom), etc.

6) Individuals who have listened to and understood the detailed explanation of the observational study and the characteristics of the investigational products, and have voluntarily signed a written informed consent agreeing to participate in the study and to comply with subject precautions during the study period

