# Evaluation Criteria and Methods, and Statistical Analysis Methods

## Endpoints

1. **Efficacy Endpoints**
2. **Primary Efficacy Endpoint**

- Change in BMI and weight at 24 weeks compared to baseline

1. **Secondary Efficacy Endpoints**
2. Change in BMI and weight at 12 weeks compared to baseline
3. Proportion of subjects achieving ≥ 5% reduction in BMI and weight at 12 and 24 weeks compared to baseline
4. Change in body composition analyzer indicators (body fat mass, visceral fat mass, muscle mass, waist/hip circumference, etc.) at 12 and 24 weeks compared to baseline
5. Change in HbA1c at 12 and 24 weeks compared to baseline
6. Change in FPG at 12 and 24 weeks compared to baseline
7. Proportion of subjects achieving HbA1c < 7% at 12 and 24 weeks compared to baseline
8. Proportion of subjects achieving HbA1c < 6.5% at 12 and 24 weeks compared to baseline
9. Proportion of subjects achieving therapeutic response [change in HbA1c (baseline HbA1c – HbA1c at each evaluation time point) > 0.5% or HbA1c < 7%] at 12 and 24 weeks compared to baseline
10. **Exploratory Endpoints**
11. Change in lipid levels (total cholesterol, LDL-C, HDL-C, triglycerides) at 12 and 24 weeks compared to baseline
12. Change in liver function markers (AST, ALT, γ-GTP) at 12 and 24 weeks compared to baseline
13. Change in renal function markers (e-CFR, UACR (Urine Albumin to Creatinine Ratio), UGCR (Urine Glucose to Creatinine Ratio)) at 12 and 24 weeks compared to baseline
14. Change in other body composition analyzer indicators (body water, intracellular water, extracellular water, extracellular water ratio, abdominal fat percentage, etc.) at 12 and 24 weeks compared to baseline
15. **Safety Endpoints**
16. Definition of an adverse drug reaction (ADR)
17. Incidence rate and number of occurrences of Serious ADRs (SADRs)
18. Adverse events of Special Interest^*^

* Hypoglycemia, urinary tract infection, genital infection, frequent urination, polyuria

1. Laboratory tests, vital signs, physical examination results

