### Primary Efficacy Endpoint

For body mass index (BMI) and weight, descriptive statistics will be presented at baseline and at 24 weeks. The change from baseline to 24 weeks will be analyzed using a Paired t-test or Wilcoxon signed rank test.

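### The protocol aims to confirm the drug's weight-loss efficacy, but a single-arm test of change against zero, with diet and exercise planned by all, shows only that weight changed; users of another SGLT-2 inhibitor are not excluded from the pooled set

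*Protocol*

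**What the plan says.** **Aim.** Protocol Section 4.1 describes a study "to confirm the weight loss efficacy and safety of Envlo Tab. or Envlomet SR Tab. over 24 weeks in patients with Type 2 Diabetes", and the synopsis uses the same verb. Section 2 says the study "aims to verify the weight reduction effects and safety of Envlo Tab. or Envlomet SR Tab".

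**Design and primary analysis.** Section 3.2 is explicit about the design: "As a single-arm observational study, the number of subjects was calculated using G*Power 3.1.9.7". The primary endpoint in Section 8.1 is "Change in BMI and weight at 24 weeks compared to baseline". For its analysis, Section 8.2 says: "The change from baseline to 24 weeks will be analyzed using a Paired t-test or Wilcoxon signed rank test". No comparator, external reference or threshold other than zero is given.

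**Who enters.** Inclusion criterion 4 (Section 3.3) requires "Individuals who plan to engage in appropriate exercise and dietary therapy for blood glucose control during the observational study period". Criterion 2 admits patients who "are about to receive Envlo Tab. or Envlomet SR Tab. for the first time". Section 4.1 opens enrolment broadly: "Regardless of whether they are currently undergoing pharmacotherapy for diabetes, all eligible patients who are considered suitable". Section 3.4 excludes recent obesity or weight-loss treatment that left weight unstable. It does not name prior SGLT-2 inhibitor use and sets no washout from it.

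**Who is analysed.** Section 8.2 defines one efficacy set: eligible, enrolled subjects with at least one dose and a post-baseline weight. It is not divided by prior therapy. Subgroup analysis is optional, and gender is the only example given.

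**The concern.** A paired test answers one question: is the mean within-patient change different from zero? Confirming a drug's efficacy requires a different question: is the change different from what these patients would have shown without the drug? With one arm, nothing in the data supplies that second quantity.

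The protocol also names a competing cause, because every subject must intend to diet and exercise over the same 24 weeks. A weight loss from that source alone could make the test significant.

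A second feature works in the other direction. Being new to Envlo or Envlomet SR is not the same as being new to SGLT-2 inhibitors. Section 1.1 puts the class effect at about 2-3 kg in the first six months. A patient moving from another drug of the class may already carry some of that loss in the baseline weight. If so, pooling dilutes the mean.

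What is at stake is the conclusion. A significant result would be reported against an aim of confirming efficacy, although the design cannot support that statement.

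**Working it through.** **Inputs from the protocol.** Section 3.2 gives a mean change of 2.5 kg, SD 10.0, effect size 0.25, power 0.95, alpha 0.05, about 210 required, and 240 recruited allowing about 15% dropout. Section 8.2 makes tests two-sided at 5%. (Section 3.2 also lists a dropout rate of 30%. That is a separate matter; 15% is used here because the text ties it to the 240.)

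**Step 1. Reproduce the plan's figure.** For a paired t-test, power = P(|T| > t(0.975, n−1)), where T is noncentral t with n−1 degrees of freedom and noncentrality (mean/SD)·√n. With mean/SD = 2.5/10 = 0.25, the smallest n reaching 0.95 is **210** (power 0.9501). The plan's number is right for this test. The calculation has no term for a comparator or for change not due to the drug.

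**Step 2. Evaluable number.** 240 × (1 − 0.15) = 204. Noncentrality is 0.25 × √204 = 3.571, and power is **0.945**.

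**Step 3. What the test will call significant.** The smallest significant mean loss is t(0.975, 203) × SD/√n = 1.972 × 10/√204 = 1.972 × 0.700 = **1.38 kg**, from any cause.

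**Step 4. No drug effect, some non-drug loss.** The losses, and the SD of 5, are assumptions. The protocol gives no figure for lifestyle loss.

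| Assumed non-drug loss | P(significant), SD 10 | P(significant), SD 5 |
|---|---|---|
| 0.5 kg | 0.11 | 0.30 |
| 1.0 kg | 0.30 | 0.81 |
| 1.5 kg | 0.57 | 0.99 |
| 2.0 kg | 0.81 | >0.99 |

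**Step 5. Prior users of the class in the pooled set.** Let a share f lose no further weight and the rest lose 2.5 kg. The pooled mean is 2.5 × (1 − f). Both f and the zero further loss are assumptions. n = 204 and SD = 10 are held fixed.

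| Assumed share f | Pooled mean | Power |
|---|---|---|
| 0% | 2.50 kg | 0.945 |
| 10% | 2.25 kg | 0.892 |
| 20% | 2.00 kg | 0.811 |
| 30% | 1.75 kg | 0.701 |

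**Step 6. Can these patients be identified?** Largely, yes. Sections 4.3 and 4.4 and the notes to the data-collection schedule record diabetes drugs taken in the 4 weeks before Visit 1. Someone who stopped an SGLT-2 inhibitor earlier than that would be missed.

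Steps 4 and 5 push in opposite directions and are not meant to be combined. Step 4 shows why a positive test does not establish a drug effect. Step 5 shows that the estimate depends on a patient mix that the plan does not separate.

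**The case against.** The strongest reply is that a single arm is normal for a registry study and that the protocol is open about it. Its wording also varies: Section 3.2 speaks of observing effects, Section 1.2 of collecting real-world evidence, and the listed primary objective in Section 2.1 is simply the change from baseline. This stands as a defence of the design. It does not defend the aim in the synopsis and Sections 2 and 4.1, which promises more than the design can give.

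Diet and exercise as an entry condition matches the approved use described in Sections 1.2 and 5. Lifestyle habits are recorded at each visit, and the exclusion for recent unstable weight limits carry-over trends. All of this stands. Drug plus lifestyle is a legitimate real-world quantity, which is why the aim should name it. Recording lifestyle does not create a comparison group.

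Four stronger readings are tempting, and the document does not support them:

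- A reader might infer that patients switching from another SGLT-2 inhibitor are in the study. The protocol never mentions switching; it only fails to exclude such patients. Their further weight change is also not stated.
- A reader might take the Dietary Habits Guide (Attachment 3) as an added intervention. Only its title is visible, and dietary habits are also a data item.
- A reader might count the lack of a planned confidence interval for efficacy as a fault. That detail is commonly left to a statistical analysis plan, which is not at hand.
- A reader might conclude that the primary set must be limited to patients new to the class. That is debatable in a study that deliberately enrols regardless of current diabetes drugs.

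An unseen analysis plan could add adjustment or strata. It cannot supply a comparator or alter the aim stated in the protocol.

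**Conclusion.** The point holds as a mismatch between the stated aim and the planned analysis. A significant paired test would show that mean weight or BMI changed over 24 weeks in patients taking the drug and planning diet and exercise. It would not confirm that the drug caused the change. This rests on the text alone and needs no assumption.

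The second part is narrower. Prior users of the class are not excluded and would be pooled, in unknown number. The loss of power from 94.5% to 81% illustrates a 20% share with no further loss at n = 204 and SD 10; with no such patients there is no dilution. The probabilities for a purely non-drug loss are likewise illustrations.

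The data would remain useful, and the sample size is correct for the test it was built on. What should change is what may be concluded, and the visibility of one subgroup.

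**What to change.** 1. In the synopsis and Sections 2 and 4.1, restate the aim as estimating the mean 24-week change in weight and BMI in patients starting enavogliflozin alongside diet and exercise. State that the test against zero will not be used to conclude that drug efficacy is confirmed.

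2. Keep the full efficacy set for the primary result. Pre-specify in Section 8.2 that this result is also reported separately for subjects with and without an SGLT-2 inhibitor in the 4-week prior-medication record, and note that this record misses earlier users.

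**Cost.** Changes of wording and one extra analysis from data already collected, with no new visits, tests or subjects. The price is a softer claim.

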## Duration of Observation Study

The study is expected to last approximately 24 months from the date of IRB approval. For each subject, the data collection period will be up to 24 weeks (6 months), during which the information specified in the study protocol will be collected. However, if circumstances arise that affect the study progress, such as difficulties in subject recruitment, the period may vary.

## Procedure and Schedule of Observational Study

### Visit Schedule

There are no mandatory visits, tests, laboratory tests, or treatments in this study. Data will be prospectively collected using medical records, investigator assessments, and laboratory test results from routine clinical visits. Each investigator will collect predefined information from subjects at baseline and during the follow-up period.

1. **Visit 1 (Baseline, Day 0)**

At the first visit (baseline), the following information will be collected:

- Obtain subject consent and assign subject enrollment number
- Inclusion/Exclusion Criteria Confirmation
- Demographic information [initials, gender, age (month and year of birth), pregnancy and breastfeeding status]
- Alcohol/Smoking/Lifestyle information
- Physical measurements (height, weight)
- Body composition analysis (include BMI, skeletal muscle mass, body fat mass, body fat percentage, etc.)
- Vital signs (systolic/diastolic blood pressure, pulse rate)
- Information on Type 2 Diabetes (Diagnosis date)
- Medical history (Past medical history within 6 months prior to enrollment (excluding the target disease) and current medical history)
- Prior medications (diabetes treatments within 4 weeks prior to enrollment) and concomitant medications (all medications, including diabetes treatments, taken at the time of enrollment).
- Laboratory tests (HbA1c, FPG, Total Cholesterol, LDL-C, HDL-C, Triglyceride, ALT, AST, Creatinine, e GFR, UACR, UGCR, etc.)
- Administration Information of Envlo Tab. or Envlomet SR Tab.

1. **Follow-Up Visits**

Follow-up visits will be conducted at 12-week intervals from the first visit (baseline) as Visit 2 (12 weeks ±2 weeks) and Visit 3 (24 weeks ±2 weeks). During follow-up visits, the following information will be collected:

- Alcohol/Smoking/Lifestyle information
- Physical measurement (weight)
- Vital signs (systolic/diastolic blood pressure, pulse rate)
- Body composition analysis (include BMI, skeletal muscle mass, body fat mass, body fat percentage, etc.)
- Concomitant medications
- Laboratory tests (HbA1c, FPG, Total Cholesterol, LDL-C, HDL-C, Triglyceride, ALT, AST, Creatinine, e GFR, UACR, UGCR, etc.)
- Administration Information of Envlo Tab. or Envlomet SR Tab.
- AEs

